### Study timeline

Each participant will be involved in the trial for a total of 28 weeks, consisting of a 4-week baseline period, 20-week post-randomisation (intervention) period, and 4-week post-intervention period. To join the trial, a participant will sign a consent form and complete a pre-trial questionnaire. Upon consent and completion of the pre-trail questionnaire participants will receive a link via SMS to download the FEEDBACK app. Once a participant downloads the FEEDBACK app and pairs the smartphone with their car (via Bluetooth), their participation in the trial will commence.

During the 4-week baseline period, the FEEDBACK app will collect data on the participant’s driving behaviours: speeding, braking, and acceleration. However, the app will not display any information to the participants during the baseline period (see Fig. 1a). After the 4-week baseline, participants will be randomised (as discussed in Sect. 2.6) into either the control group or intervention group for the next 20-week intervention period.

#### Control group

During the 20-week intervention period, participants randomised to the control group will be entered into a weekly draw to win an e-voucher worth AU$100 and will receive weekly SMS messages announcing the winner of the weekly draw. Weekly SMS messages will also include a reminder to keep location tracking enabled for the FEEDBACK app. Throughout the trial, the FEEDBACK app will not display any information to the control group participants as shown in Fig. 1a.

#### Intervention group

The intervention group will be entered into the same weekly draw and in addition, will receive personalised driver feedback and financial incentives as described below.

*Personalised driver feedback*: Participants in the intervention group will be able to view feedback on their driving performance in the FEEDBACK app. This feedback is provided in the form of a ‘DrivePoints’ score, which is an average of scores calculated for speed, braking, and acceleration captured via mobile telematics for driving trips over a week. The DrivePoints score ranges in value between 0 and 5 and is colour coded as dark green, light green, yellow, amber and red, where dark green indicates the lowest level of at-risk driving, light green, yellow and amber indicate increasing levels of at-risk driving, and red indicates the highest level of at-risk driving. For example, for weeks with repeated instances of speeding, harsh braking or acceleration, the DrivePoints score will be classified as yellow, amber or red, depending upon the frequency and severity of each behaviour. For weeks with low or no unsafe driving, the DrivePoints score will be classified as light green or dark green. Figure 1b shows an example of how the DrivePoints scores will be visible to the participants through the FEEDBACK app.

Each month the intervention group will receive an SMS containing their DrivePoints score for that month and a target score (referred to herein as the ‘safe driving target’) for the following month. Safe driving targets are calculated per participant and based on their driving behaviour in the month prior as indicated by the number of red, yellow, amber, light green and dark green DrivePoint scores. For instance, if a driver receives mostly green DrivePoints scores and no red scores but some yellow and at least one amber DrivePoint score in a given month, then their safe driving target in the following month would be to maintain their record of mostly green and no red DrivePoint scores but to also avoid getting any amber scores and to receive no more than one yellow score. The ‘safe-driving target’ for the first month (Month 1) will be personalised using the data from the baseline period. For every other month, the safe-driving target will be calculated based on driving behaviour in the month prior. Table 1 defines rules for calculating safe driving targets.

**Fig. 1 Fig1:**
[figure not shown]
An illustration of the FEEDBACK app. (**a**) FEEDBACK app view during the baseline and post-intervention periods for both groups and during the intervention period for the control group. (**b**) FEEDBACK app showing the ‘DrivePoints’ scores and feedback for the intervention group during the intervention period

**Table 1 Tab1:** Calculations of the safe driving target for each month during the intervention period^1^

Driving performance in the previous month	Safe-driving target for the current month
No trips	No more than one yellow, amber or red DrivePoint scores, *or* repeat of previous month’s safe-driving target, whichever is the most stringent.
Only dark green DrivePoint scores	Only dark green DrivePoint scores
Only dark green and light green DrivePoint scores	Only dark green DrivePoint scores
At least one yellow, but all other DrivePoint scores were light green or dark green	Only dark green and light green DrivePoint scores with no more than one light green
Any number of yellow, light green and dark green DrivePoint scores, at least one amber DrivePoint score, and no red DrivePoint scores	Only yellow, light green and dark green DrivePoint scores, with no more than one yellow
Any number of amber, yellow, light green and dark green DrivePoint scores, with one red DrivePoint score	Only amber, yellow, light green and dark green DrivePoint scores, with no more than one amber
Any number of amber, yellow, light green and dark green DrivePoint scores, with two red DrivePoint scores	Any number of amber, yellow, light green and dark green DrivePoint scores, with only one red DrivePoint score
Any number of amber, yellow, light green and dark green DrivePoint scores, with at least three red DrivePoint scores	Any number of amber, yellow, light green and dark green DrivePoint scores, with no more than two red DrivePoint scores

^1^ Decision rules specified in Table 1 will be applied in each month of the intervention period subject to two constraints. First, the ‘safe-driving target’ for a given month could not be less stringent than the participant’s ‘safe-driving target’ in any prior month. Second, the floor for acceptable driving behaviour could only be specified in the first month of the intervention period to ensure that penalties were applied for high and persistent levels of unsafe driving. The application of these constraints and the effects of the incentive should result in a progressive lowering of the threshold over the 20-week intervention period to incentivise further improvements in driving behaviour

#### Personalised financial incentives

Financial incentives will be structured as penalties for risky driving; levied as monthly deductions from an upfront payment of AU$120 deposited to a virtual ‘safe driving account’. This approach is designed to mimic a PAYD implementation, where financial penalties are typically framed as periodic deductions from an (earned) discount on PAYD insurance premiums. If a participant fails to meet their safe driving target for a given month, AU$24 will be deducted from their safe driving account that month. Participants will receive no penalty for risky driving provided that their driving behaviour remains consistent with achievement of their safe driving target (e.g., yellow and amber DriveScores would not incur a penalty if the monthly safe driving target is no more than one red DriveScore). Each week, the intervention group participants will receive an SMS updating them on the weekly draw, their current DrivePoints score and safe driving target, and safe driving account balance (see Table 2).

**Table 2 Tab2:** An example SMS message a participant in the intervention group receives during the intervention period

Thank you for completing another month in the FEEDBACK trial. Your safe driving account currently has a balance of $**120**, and your new safe driving target is: **only yellow, light, or dark green DrivePoints scores, with no more than ONE yellow** over the next four weeks. If you fall short of this safe-driving target, you will lose $24 from your safe-driving account.	

After the 20-week intervention period, there will be a 4-week post-intervention period. During this time, participants will not be entered into weekly draws. The intervention group will also not be able to view information in the FEEDBACK app, nor receive SMS messages with updates on their DrivePoints scores, safe driving targets, or safe driving account balance. However, they will receive an SMS message reminding them to keep location tracking enabled for the FEEDBACK app. Mortimer et al.’s [7] study illustrates how a target behaviour may decay or reverse once an intervention concludes, with findings showing behavioural reversals once feedback and incentives are ‘switched off’. Monitoring participants’ driving behaviour during this post-intervention period will reveal whether any changes in participants’ driving performance persist after the intervention ceases.

At the end of this post-intervention period, participants will receive a link to the post-trial questionnaire. Upon completing the questionnaire, the control group will be entered into one final draw. The intervention group will be able to receive the remaining funds of their safe driving accounts via an e-voucher. Figure 2 illustrates an overview of the aforementioned activities conducted during each stage of the trial timeline.

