### Sample size

Statistics from QLD and NSW in Australia in 2022 suggest there is a large population of P1 licence holders aged 18–20 years to sample from: 32,151 young drivers in QLD [38] and 42,039 in NSW [39]. Based on crash statistics for QLD from 2016 to 2022, the incidence of a young P1 licence holder having a police-reported crash of any type during a 6-month period is approximately 3% [40], with similar patterns expected across NSW and WA. Based on the findings of recent research [7, 8] the FEEDBACK trial intervention is expected to lower the proportion of a police-reported crashes from 3 to 1.5%.

To detect a 1.5% absolute reduction in the incidence of young drivers having a police-reported crash of any type during the 24-week intervention and post-intervention periods, from 3% in the control group to 1.5% in the intervention group (or 0.5 relative risk), using a two-sided type I error of 5% and a power of 80%, a total of 3,068 participants are required. Allowing for a 15% non-response rate due to drivers who may choose to withdraw from the study, turn off their phones, or delete the smartphone app, 1,805 participants per arm, or a total of 3,610 participants, will be recruited to participate in the trial.

To achieve adequate participant enrolment and reach the target sample size, recruitment strategies will be carried out in partnership with government stakeholders. The transport departments from the three states of Western Australia, Queensland, and New South Wales will assist with advertising the trial via several media channels, including social media, associated websites, and advertising boards in licencing centres.

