#### Secondary outcomes

The DrivePoints score will be analysed using a constrained longitudinal data analysis (cLDA) model [42]. The response will consist of all DrivePoints scores (scores at baseline, at weekly intervals until 24 weeks post-randomisation) and the model will include factors representing treatment, time (categorical), and treatment-by-time interaction, with the restriction of a common baseline mean across treatment groups.

The total number of police-reported crashes of any type during the 24-week intervention and post-intervention periods will be analysed using a Poisson regression model. Whether a driver has a self-reported crash during the 24-week intervention and post-intervention periods will be analysed using a log-binomial regression model. Driving behaviours (i.e., binary outcomes – speeding, harsh braking, and harsh acceleration at baseline and at weekly intervals from week 4 to week 28) will be analysed using mixed-effects Poisson regression models with robust standard errors. All analysis models will be adjusted for stratification factors, study site and sex.

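### Intervention drivers alone lose money for recorded risky driving, and the tracking reminders differ by arm as written, so the telematics outcomes can be selectively unrecorded in one arm

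*Protocol article*

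**What the plan says.** All references are to the protocol article.

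- **Penalty.** Personalised financial incentives: "If a participant fails to meet their safe driving target for a given month, AU$24 will be deducted from their safe driving account". The account opens at AU$120 and exists only in the intervention arm.
- **What the penalty depends on.** Under Intervention group, the DrivePoints score is a weekly average of speed, braking and acceleration scores over trips captured by the app. Table 1 expresses most targets as a cap on poorer weekly scores. Its row for a month without trips sets the following target; no deduction is stated for such a month.
- **Tracking reminder during the 20 intervention weeks.** Control group: "Weekly SMS messages will also include a reminder to keep location tracking enabled for the FEEDBACK app". Intervention group: "Each week, the intervention group participants will receive an SMS updating them on the weekly draw, their current DrivePoints score and safe driving target", followed by the account balance. No tracking reminder appears in that list or in the example message in Table 2.
- **Tracking reminder after the intervention.** Following a sentence about what the intervention group no longer sees, the text says "they will receive an SMS message reminding them to keep location tracking enabled for the FEEDBACK app".
- **Safeguards.** Aims and eligibility criteria makes enabled location tracking part of engagement for both arms, described next to the prize draw. The withdrawal paragraph after Fig. 2 provides a staff call when a participant's telematics data stop arriving.
- **Analysis.** Secondary outcomes: "The DrivePoints score will be analysed using a constrained longitudinal data analysis (cLDA) model"; the driving behaviours are analysed with mixed-effects Poisson models. The missing-data statement and the multiple imputation analysis concern the primary crash outcome only.

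**The concern.** The same app both delivers the penalty and measures the outcome. A trip the app does not capture cannot lower the score, cannot breach a target and cannot cost AU$24. Intervention drivers are told their score, target and balance every week, so they can see when leaving a trip unrecorded would save money. Control drivers have no such motive. If the prompt to keep tracking on is also weaker in the intervention arm, the arm with the motive to hide gets the lesser reminder.

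At stake are the DrivePoints and driving-behaviour results, both named secondary hypotheses. An apparent improvement could come partly from safer driving and partly from less recording of unsafe driving, and the two would look alike. The persistence analysis is exposed as well: when penalties stop, so does the motive to hide, and recorded scores could then worsen and resemble the behavioural reversal that the protocol anticipates.

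**Working it through.** **1. The protocol's own figures.** Sample size states "using a two-sided type I error of 5% and a power of 80%, a total of 3,068 participants are required", for 3% against 1.5%. With pooled variance under the null and mean proportion 0.0225:

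n = [1.960 × √(2 × 0.0225 × 0.9775) + 0.842 × √(0.03 × 0.97 + 0.015 × 0.985)]² / 0.015², which rounds up to 1,534 per arm, or 3,068 in total.

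Inflation: 1,534 / 0.85 = 1,805 per arm, or 3,610. Both reproduce exactly and are not in dispute. The penalty arithmetic is also consistent: 120 / 24 = 5 deductions and 20 / 4 = 5 months.

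**2. Reminders side by side, as written.**

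| Period | Control | Intervention |
|---|---|---|
| 20 intervention weeks | weekly reminder stated | not among listed SMS contents |
| 4 post-intervention weeks | not separately described | reminder stated (most natural reading) |

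**3. What the safeguards reach.** The staff call is triggered when data cease, so it addresses complete switch-off. The engagement condition applies equally to both arms. Neither would detect one unrecorded trip in a week that contains other recorded trips.

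**4. What the models can correct.** cLDA and mixed-effects Poisson models give valid results with missing weeks if the missingness is ignorable. That is a property of the methods; the protocol does not state it. A hidden trip drops out of the weekly average and the week remains observed with a better score. This is biased measurement, so there is no missing value for these models, or for imputation of missing weeks, to act on.

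**5. Size under assumptions.** The protocol gives no DrivePoints SD, trip count or rate of risky trips, so every input here except 1,534 per arm is assumed. There is no true effect and controls hide nothing.

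(a) *Direct bias.* If a share x of intervention driving is unrecorded and is D SDs worse than the recorded driving, bias = x × D. With SD = 1, the standard error of a single-week arm difference is √(2 / 1,534) = 0.036.
- x = 5%, D = 1: bias 0.05, shift 0.05 / 0.0361 = 1.38, two-sided rejection probability 28%.
- x = 10%, D = 0.5: bias 0.05, again 28%.
- x = 10%, D = 1: bias 0.10, shift 2.77, rejection probability 79%.

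(b) *Hidden trips, weekly mean score (simulation).* 10 trips a week, the worst 20% counted as risky, between-driver SD 0.6, within-driver trip SD 1; a fraction f of risky trips is hidden.

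| f | Share of all trips hidden | Bias (weekly SD) | Rejection probability, one week |
|---|---|---|---|
| 5% | 1% | 0.02 | 7% |
| 10% | 2% | 0.04 | 17% |
| 20% | 4% | 0.08 | 54% |
| 30% | 6% | 0.12 | 89% |

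No week became missing in any of these runs.

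(c) *Hidden trips, weekly binary behaviour.* With k trips a week, each risky with probability p, the control proportion is 1 − (1 − p)^k and the intervention proportion is 1 − (1 − p(1 − f))^k. For k = 5, p = 0.2, f = 10%: 0.672 against 0.629, a spurious risk ratio of 0.94 and a rejection probability of 71%. Over k = 5 or 10 and p = 0.1 to 0.3, f = 5% gives 15% to 28%, f = 10% gives 48% to 80%, and f = 20% gives at least 97%.

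**The case against.** The strongest reply has five parts.

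*Nothing in the protocol shows that drivers will hide trips.* This stands. A reader might infer that the telematics outcomes are selectively unrecorded. The documents support only that they can be. The protocol does expect some loss of recording ("Allowing for a 15% non-response rate due to drivers who may choose to withdraw from the study, turn off their phones"), but it does not tie that loss to arm or to risk.

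*The reminder difference rests partly on silence.* This also stands in part. The list of intervention SMS contents does not say that a reminder is excluded, Table 2 is only an example, and the pronoun in the post-intervention sentence could mean all participants. A condensed article is weak evidence of a deliberate difference. Uneven reminders alone would also not make recording depend on risk. What remains is that the sections differ as written and need reconciling.

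*Missing-data sensitivity analyses belong in the statistical analysis plan.* Agreed. A reader might take their absence for the telematics outcomes as a fault, but the protocol promises a separate detailed plan. In any case, a tipping-point analysis for missing weeks would not touch hidden trips.

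*The safeguards, and the rule that targets never loosen, discourage prolonged switch-off.* They do, but they leave single trips untouched.

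*The magnitude is assumed.* Correct. If 20% of trips are risky, losing 5% of driving, all of it risky, means hiding a quarter of all risky trips (0.05 / 0.20) on average across the arm. At a bias of 0.05 SD, 72% of single-week contrasts would still be non-significant.

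**Conclusion.** The point holds as a foreseeable risk created by the design. The motive not to record risky trips exists in one arm only, the stated safeguards do not detect single hidden trips, and the planned models cannot correct the flattering weekly scores that result. Any such bias would favour the intervention while penalties are in force.

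Its size cannot be derived from the protocol. Under the assumed SD of 1 and 1,534 per arm, a bias of 0.05 to 0.10 SD gives a 28% to 79% false-positive probability for a single-week contrast. The hidden-trip illustration for the score runs from 7% to 89% depending only on the assumed hiding rate. These figures show sensitivity and are not a forecast.

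The exposed results are DrivePoints, the driving behaviours and the persistence analysis. A reader might infer that the trial's main conclusion is at risk; the documents do not support that. Under Crash data, police-reported crashes come from state records for all drivers, blind to group, and do not depend on the app.

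**What to change.** 1. **Reminders.** Send the same tracking reminder to both arms in every week of the intervention and post-intervention periods, and reconcile the Control group section with Personalised financial incentives. Cost: SMS wording.
2. **Recorded exposure by arm.** Compare recorded trips, distance and duration per week between arms, and interpret the DrivePoints and behaviour effects in light of that comparison. Telematics and DrivePoints shows that trip duration and distance are already collected, so the cost is one descriptive analysis. An odometer question in each existing questionnaire is an optional rough check over the whole trial. Its downsides are noise where cars are shared and the inability to isolate the intervention period.
3. **Unrecorded driving.** State how months with little or no recorded driving count against the safe driving target. Cost: a clarifying sentence alongside Table 1 and the deduction rule.

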**Fig. 2 Fig2:**
[figure not shown]
An overview of the FEEDBACK Trial illustrating the activities during each stage of the trial: 4-week baseline, 20-week post-randomisation (intervention) and 4-week post-intervention period

Participants can withdraw from the trial at any time but will not receive financial compensation thereafter. To withdraw, a participant can contact one of the trial coordinators via email. If a participant does not inform the trial coordinators of their withdrawal but the research team no longer receives telematics data from a participant, a research staff member will call the participant to confirm whether the participant has removed the FEEDBACK app or disabled location services and whether they still intend to participate in the trial.

### Hypotheses and outcome measures

The **primary hypothesis** will assess whether personalised safety feedback and personalised financial incentives reduce the incidence of police-reported crashes of any type during the 24-week intervention and post-intervention periods. The primary outcome is a police-reported crash over the 24-week intervention and post-intervention periods. The research team will obtain data on police-reported crashes using drivers’ licence numbers provided by participants in the pre-trial questionnaire.

The **secondary hypotheses** will assess the effects of personalised feedback and financial incentives on:

Reducing the incidence of self-reported crashes by young drivers.Improving drivers’ safety scores (‘DrivePoints’ scores) from baseline.Reducing crash risk behaviours identified by speeding, harsh braking, hard acceleration, and drowsy driving from baseline.

The **outcomes** to assess the secondary hypotheses are:

Self-reported involvement in a crash that took place during the 24-week intervention and post-intervention periods that resulted in damage to their own or someone else’s vehicle.DrivePoints score at baseline and at weekly intervals through to week 28.Driving behaviours, namely:
Speeding (defined as 10 km/h over the speed limit).Harsh braking (sudden braking in which items in the vehicle would move around, defined in telematics technology as a -0.5 g force).Hard acceleration (rapid acceleration exceeding a 0.25 g force).

